The aim of this randomized, controlled trial is to evaluate the efficacy of the PAHC questionnaire when used routinely in daily clinical cancer genetics practice in: (1) facilitating communication during genetic counseling sessions about relevant psychosocial issues; (2) increasing genetic counselors’ awareness of the psychosocial problems of their counselees; and (3) facilitating the appropriate management of these cancer genetic-specific psychosocial problems. Specifically, our primary research hypotheses are that the use of the PAHC questionnaire during genetic counseling will:

(1) increase significantly the number of psychosocial issues discussed during genetic counseling sessions;

(2) increase significantly the genetic counselors’ awareness of the psychosocial problems experienced by their counselees; and

(3) improve significantly the management of cancer genetic-specific psychosocial problems as evidenced by the referrals to psychosocial care and/or to sources of information about psychosocial issues. Additionally, we hypothesize that the routine use of the PAHC questionnaire will:

(4) increase significantly the number of discussed issues initiated by the counselor;

(5) increase significantly counselees’ satisfaction with the counseling process;

(6) decrease significantly counselees’ levels of cancer worry and distress during and after the genetic counseling process;

(7) decrease significantly the cancer genetic-specific problems experienced by the counselee after the genetic counseling process; and

(8) *not* increase significantly the total duration of the genetic counseling session.

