### Study sample

The study sample will be composed of 264 counselees who request genetic counseling at either The Netherlands Cancer Institute in Amsterdam or the University Medical Center Utrecht. Counselees will be excluded from the study if they are younger than 18 years of age, do not have basic fluency in the Dutch language or are participating in another study that would interfere with the current study.

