#### Sociodemographic and clinical data

The counselees’ age, gender, marital status, education level, number and age of children, and use of psychosocial services in the past and during the study, will be obtained via the self-report questionnaires (Table 
1). Data on whether (s)he was diagnosed with cancer in the past and, if so, at what age, whether there is a known gene mutation in the family, the counselees’ genetic test results, and the number of genetic counseling sessions will be extracted from the medical records.

**Table 1 T1:** Content and timing of study measures

	**Content of the measurement**	**Timing of measurement**

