#### Management of psychosocial problems

The audiotapes of the counseling sessions will also be used to evaluate how the counselees’ psychosocial problems are managed. Specifically, the study-specific checklist will be used to code whether counselees were referred to additional sources of information about how to deal with psychosocial problems (e.g., websites or written materials) or to additional psychosocial counseling. The counselees will be asked to report their actual use of psychosocial services.

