#### Main research hypotheses

We will evaluate group differences in the number of psychosocial issues discussed during the genetic counseling sessions using analysis of (co)variance. We will assess counselors’ awareness of their counselees’ psychosocial problems by calculating the agreement between counselees’ and counselors’ on their ratings, per domain, of the psychosocial problems experienced by the counselees. We will calculate an Intraclass Correlation Coefficient (ICC2.1.A
[34]) per domain for both the intervention and control group. Group differences will be assessed by treating the ICC’s as Pearson correlation coefficients and using Fisher’s r-to-z transformation to test for statistical differences per domain. Analysis of (co)variance will also be used to evaluate group differences in referral to additional information sources and/or referral to psychosocial care services, and the actual use of such services.

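### The use component of the management outcome is not limited to care started after counseling, and recorded past use enters the model only if the arms happen to differ at baseline

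*Protocol article*

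**What the plan says.** All of this is in the protocol article.

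- **Who can enter.** Study sample lists three exclusions: "Counselees will be excluded from the study if they are younger than 18 years of age", or if they "do not have basic fluency in the Dutch language or are participating in another study that would interfere with the current study". Current psychosocial care is not among them.
- **How management is measured.** Under Management of psychosocial problems, referrals come from the audiotapes: "the study-specific checklist will be used to code whether counselees were referred to additional sources of information" or to psychosocial counseling. Use is then added by self-report: "The counselees will be asked to report their actual use of psychosocial services".
- **How it is analyzed.** Main research hypotheses assigns analysis of (co)variance to "group differences in referral to additional information sources and/or referral to psychosocial care services, and the actual use of such services". No covariate is named for this outcome.
- **What is recorded.** Sociodemographic and clinical data says that "use of psychosocial services in the past and during the study, will be obtained via the self-report questionnaires".
- **When baseline variables are adjusted for.** Comparability of intervention and control group adjusts only for characteristics on which the arms prove statistically different. Secondary research hypotheses, by contrast, fixes the previous score as covariate for cancer worries and distress in advance.
- **What hypothesis 3 claims.** Background states that better management will be shown "as evidenced by the referrals to psychosocial care and/or to sources of information about psychosocial issues". Use of services is not mentioned there.

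**The concern.** Care that was running before the first session cannot have been caused by a referral made in that session. If such care counts as use, a counselee already in therapy is a user in either arm. The difference then reflects only those not yet in care, while the extra users raise the variance at these low rates. A real increase in newly started care could be missed.

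The planned adjustment rule gives little protection. Under 1:1 randomization a statistically significant baseline difference arises mostly by chance, so past use would usually stay out of the model however well it predicts use during the study. Whether a covariate is worth including depends on how well it predicts the outcome, not on whether it happens to be imbalanced.

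**Working it through.** **The plan's own figure.** Sample size and power calculations uses d = 0.4, power 0.80 and alpha 0.05. Taking alpha as two-sided, n = 2(1.96 + 0.84)²/0.4² ≈ 98 per arm by the normal approximation, and 99 with the t correction. The total is 198, and 198/0.75 = 264, or 132 per arm at entry. This reproduces. It is sized on communication, not on service use.

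**Inputs that the article does not give (assumptions).** Newly started use among those not in care is p_C = 8% (control) and p_T = 20% (intervention). A share q of each arm is already in care. Those counselees report use throughout and start nothing new.

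**Formulas.**
- Any use: P = q + (1 − q)p.
- Newly started use, everyone in the denominator: P = (1 − q)p.
- The difference is (1 − q)(p_T − p_C) under both definitions.
- SE = √{[P_C(1 − P_C) + P_T(1 − P_T)]/132}; power = Φ(difference/SE − 1.96).

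**Worked case, q = 20%.**
- Any use: 26.4% vs 36.0%, difference 0.096. SE = √[(0.1943 + 0.2304)/132] = 0.0567. z = 1.69, power = Φ(−0.27) = 0.39.
- Newly started: 6.4% vs 16.0%, difference 0.096. SE = √[(0.0599 + 0.1344)/132] = 0.0384. z = 2.50, power = Φ(0.54) = 0.71.

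**Range, 132 per arm.**

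| Already in care (q) | Any use, control vs intervention | Difference (points) | Power, any use | Power, newly started |
|---|---|---|---|---|
| 0% | 8.0% vs 20.0% | 12.0 | 0.81 | 0.81 |
| 2% | 9.8% vs 21.6% | 11.8 | 0.76 | 0.80 |
| 5% | 12.6% vs 24.0% | 11.4 | 0.68 | 0.79 |
| 10% | 17.2% vs 28.0% | 10.8 | 0.56 | 0.76 |
| 20% | 26.4% vs 36.0% | 9.6 | 0.39 | 0.71 |
| 30% | 35.6% vs 44.0% | 8.4 | 0.29 | 0.64 |

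Two parts of the loss should be kept apart. At q = 20%, the fall from 0.81 to 0.71 cannot be avoided while everyone stays in the denominator, because counselees already in care cannot newly start. The fall from 0.71 to 0.39 comes from the added variance, and this is what the outcome definition controls.

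**Other assumed rates, q = 20%, 132 per arm.** For 10% vs 25%, power is 0.55 (any) and 0.81 (new). For 5% vs 15%, it is 0.31 and 0.68.

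**Phase II, 99 per arm, q = 20%, 8% vs 20%.** Each z is multiplied by √(99/132) = 0.866. Any use: 1.69 × 0.866 = 1.47, power 0.31. Newly started: 2.50 × 0.866 = 2.17, power 0.58.

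**What the covariate alone could recover.** Suppose any use is kept but adjusted for being in care at baseline. In this idealized setting the residual variance is about (1 − q)p(1 − p): 0.8 × 0.08 × 0.92 = 0.0589 and 0.8 × 0.20 × 0.80 = 0.1280. SE = √(0.1869/132) = 0.0376, z = 0.096/0.0376 = 2.55, power about 0.72. That is a ceiling. Past use is only a proxy for current care, so the real recovery would be partial.

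**The case against.** The strongest reply is that the article never says it counts any use. The use it compares is of the services just named as objects of referral, so uptake after referral is a possible reading. The article also records past use separately from use during the study. It is a condensed report, and item wording, start dates and coding may well be settled in questionnaires or a full protocol that are not shown. Analysis of (co)variance leaves room for a covariate, and the comparability rule does not forbid others.

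Much of this stands. A reader might infer that the plan definitely scores earlier therapy as an outcome event, but the text supports only that the definition is unqualified. A reader might also infer that hypothesis 3 as a whole is weakened. It is not: that hypothesis names referrals, these are coded from the audiotapes, and earlier care is not counted as a referral. Nor are the rates known. With 2% in care the loss is about 0.04 in power, and the trial claims no power for service use.

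The adjustment rule is what the reply does not remove. It is stated, it makes use of a recorded predictor depend on chance imbalance, and it differs from the prespecified covariate that the same article gives to worry and distress.

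**Conclusion.** The point holds for the use component of primary outcome 3. The article tests an unqualified measure of service use in a population that may include counselees already in care. It ties adjustment for recorded past use to a significance test at baseline.

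If ongoing care is counted, the cost is sensitivity. Under assumed new use of 8% vs 20% and 132 per arm, it is small at 2% in care (0.80 to 0.76) and large at 20% (0.71 to 0.39). The true size is unknown because the article gives neither the share in care nor the rates of use.

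The result does not extend further. Randomization puts the same expected share of ongoing care in both arms, so there is no bias toward either and no route to a false positive. The audiotape-coded referrals and the sample size stand. This is a worthwhile, nearly free improvement, not a flaw that threatens the trial.

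**What to change.** 1. **Main research hypotheses:** name baseline psychosocial service use, taken from the questionnaire completed before randomization, as a covariate for the use outcome whether or not the arms differ on it. This matches the treatment of worry and distress under Secondary research hypotheses.
2. **Management of psychosocial problems:** define the use outcome as psychosocial care newly started after the relevant session (the first session for phase I, the telephone session for phase II). Keep all randomized counselees in the denominator, including those already in care, and report any use descriptively.

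The cost is one sentence in each section. The questionnaires are not shown; if they lack them, they would need an item on current as well as past use at baseline, and one on use new since counseling at T1 and T2. These are best asked during the trial, since start dates could later be recovered only by recall. No extra participants or procedures are needed.

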#### Secondary research hypotheses

We will employ analysis of (co)variance to evaluate group differences in the frequency of with which the genetic counselor initiated the discussion of psychosocial issues. Analysis of (co)variance will also be used to evaluate group differences in the amount of counseling time spent discussing psychosocial issues, and the total length of the counseling session. To evaluate group differences in cancer worries and general distress, we will use analysis of covariance, with the previous scores on these questionnaires as covariate. Logistic regression analysis will be used to evaluate differences between groups in the prevalence of cancer genetics-specific problems. Group differences in satisfaction with the genetic counseling process will be examined with Student’s t-tests and chi square tests, where appropriate. Intervention group and counselor satisfaction with the intervention will be reported descriptively.

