### Intervention group procedure

Within the Netherlands, individuals seeking cancer genetic counseling routinely undergo a first consultation with a genetic counselor or a clinical geneticist and, when opting for a DNA-test, a final counseling session during which the DNA-test results are disclosed to the counselee. If indicated, screening recommendations for the patient and relatives are discussed within these sessions. The study intervention will take place within this standardized process, at the time of the first face-to-face genetic counseling session (phase I), and by telephone 4 weeks after the final face-to-face counseling session (phase II). The participants in the intervention group will be asked to complete the PAHC questionnaire either via the internet or, if preferred, by mail shortly before the face-to-face and the telephone follow-up counseling sessions. The counselee’s responses to the PAHC questionnaire will be made available to the genetic counselor prior to the counseling sessions.

The PAHC questionnaire consists of 26 questions addressing psychosocial problems and worries that are specifically relevant to counselees within the cancer genetics counseling and testing setting. The content of the PAHC questionnaire is organized into the following six domains: (1) hereditary predisposition; (2) family- and social issues; (3) practical issues; (4) general emotional issues; (5) cancer-specific issues; and, for those who have children 6) children-specific issues. The number of items per domain varies between 2 and 7. All 26 items are scored on a 4-point, Likert-type scale ranging from 1 (“not at all”) to 4 (“very much”). The PAHC questionnaire is supplemented by the Distress Thermometer (DT), a visual analogue scale ranging from 0–10 (no distress-severe distress). The timeframe of the PAHC questionnaire and the DT is the previous week. Per problem domain assessed by the PAHC questionnaire, the respondent is asked to indicate whether (s)he would like to receive professional psychosocial support
[25].

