### Timing and content of study measures

Counselees will be asked to complete questionnaires at: (1) baseline, prior to randomization; (2) approximately 4 weeks following the first genetic counseling session, before the final counseling session takes place; and (3) approximately 4 months after the telephone-based counseling session.

The counselors will be asked to complete a baseline questionnaire at the start of the study, a checklist at the end of each counseling session, and a final questionnaire at the end of the study. Both the in-person and the telephone-based genetic counseling sessions will be audiotaped by two independent raters ([name]) for purposes of content analysis (see below). Inter-rater reliability will be assessed by double coding 10% of the audiotaped sessions, equally divided between the intervention group and control group sessions.

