**Counselees**		
*Baseline (first) questionnaire*	Cancer worries	Before randomization
	General distress	
	Demographic data	
*Second questionnaire (T1)*	Evaluation of screening instrument	4 weeks after genetic counseling, before final consult, end of phase I
	Evaluation of counselor	
	General distress	
	Need for extra support	
	Cancer worries	
*Third questionnaire (T2)*	Specific psychosocial problems	4 months after the telephone call,
	Need for extra support	end of phase II
	Cancer worries	
	Evaluation of screening instrument	
	Satisfaction	
	General distress	

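### Cancer worry and distress at T2 are adjusted for the previous score, which read literally is a post-intervention measurement; the covariate should be named as baseline

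*Protocol article*

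**What the plan says.** Hypothesis (6) in the Background of the Protocol article is that routine use of the questionnaire will "decrease significantly counselees’ levels of cancer worry and distress during and after the genetic counseling process".

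CWS and HADS are collected three times (Timing and content of study measures; Table 1):

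- first at "baseline, prior to randomization";
- then at T1, which Table 1 places "4 weeks after genetic counseling, before final consult, end of phase I";
- then at T2, "approximately 4 months after the telephone-based counseling session".

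Under Intervention group procedure, feedback to the counselor is given twice: at the first face-to-face session, so before T1, and at the telephone session, so between T1 and T2.

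The analysis rule for both scales is one clause under Secondary research hypotheses: "we will use analysis of covariance, with the previous scores on these questionnaires as covariate". It does not say which previous score applies at which time point. Separately, Statistical analyses promises intention-to-treat analysis and omits data from participants who return the first follow-up questionnaire after their final session.

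**The concern.** At T1 there is only one earlier score, the pre-randomization baseline, and adjusting for it is standard and sound. At T2 there are two, and the nearer one is T1. T1 comes after randomization and after the first delivery of the intervention, so the intervention may have changed it.

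A T2 model that includes T1 compares participants who reached the same score after phase I, not the groups as randomized. Whatever phase I has achieved by T1, and whatever of that persists, is partly credited to the covariate instead of to the arm. Hypothesis (6) speaks of worry and distress during and after the whole process, which is a total effect.

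A second consequence follows. If T1 is the covariate, a complete-case ANCOVA also loses the T2 record of anyone whose T1 score is missing or has been omitted for late return. That sits badly with the intention-to-treat statement.

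**Working it through.** **Inputs from the article.** Sample size and power calculations gives power 0.80, alpha 0.05 and d = 0.4, hence 99 per arm and 198 in total. It then assumes 25% will have no second phase, hence 264 recruited. Taking alpha as two-sided, 2(1.960 + 0.842)² / 0.4² = 98.1, which rounds up to 99 per arm; 198 / 0.75 = 264. Both figures reproduce. They concern communication about psychosocial issues. The article states no effect size or power for CWS or HADS.

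**Assumptions.** The article gives no correlation between time points. I take equal SDs (set to 1), a common within-arm correlation r from 0.3 to 0.8, and 99 per arm at T2. I borrow d = 0.4 for illustration and assume the effect is the same at T1 and T2 (fully sustained).

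**Formulas.** Let d1 and d2 be the effects at T1 and T2.

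- Baseline as covariate: expected estimate d2; residual SD √(1 − r²).
- T1 as only covariate: d2 − r·d1; residual SD √(1 − r²). With d1 = d2 = d this is d(1 − r), so the share removed is r.
- Baseline and T1 both: the T1 coefficient is r/(1 + r), so the estimate is d2 − d1·r/(1 + r); residual SD √(1 − 2r²/(1 + r)).
- Power: Φ(estimate / (residual SD × √(2/99)) − 1.96).

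**Worked case, r = 0.7.** The residual SD is √(1 − 0.49) = 0.714 and the standard error is 0.714 × √(2/99) = 0.1015. With baseline, 0.40/0.1015 = 3.94, giving power 98%. With T1 only, the estimate is 0.40 × 0.3 = 0.12 and 0.12/0.1015 = 1.18, giving power 22%.

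| r | Baseline only: estimate, power | T1 only: estimate, power, share removed | Both: estimate, power, share removed |
|---|---|---|---|
| 0.3 | 0.40, 84% | 0.28, 54%, 30% | 0.31, 65%, 23% |
| 0.5 | 0.40, 90% | 0.20, 37%, 50% | 0.27, 63%, 33% |
| 0.7 | 0.40, 98% | 0.12, 22%, 70% | 0.24, 72%, 41% |
| 0.8 | 0.40, 99.7% | 0.08, 15%, 80% | 0.22, 83%, 44% |

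A simulated data set of 400,000 at r = 0.7 with a true effect of 0.40 gave 0.40, 0.12 and 0.24 for the three models, in agreement.

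**Two variations.**

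- *Unequal correlations, both scores in the model.* With assumed values of 0.6 (baseline–T1), 0.7 (T1–T2) and 0.55 (baseline–T2), the T1 coefficient is (0.7 − 0.6 × 0.55)/(1 − 0.6²) = 0.37/0.64 = 0.58, so 58% of a sustained effect is removed.
- *A fading effect, d1 = 0.4 and d2 = 0.2, T1 only.* The estimate is 0.2 − 0.4r: 0.08 at r = 0.3, zero at r = 0.5 and −0.12 at r = 0.8, a reversal of sign.

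**What is kept.** Write d2 as the persisting phase I part plus an increment e from phase II. Since e arises after T1, it passes through d2 − r·d1 in full. Only the part already visible at T1 is discounted.

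**The case against.** The strongest objection is that the article never names T1 as the T2 covariate. The plural could mean the earlier baseline scores, both earlier scores, or the latest score on each of two questionnaires, and a condensed article may leave the detail to a plan that is not shown. This stands in part: a reader might infer that the plan definitely adjusts T2 for T1, and the text does not go that far. But the article does state a rule. It uses the word *baseline* elsewhere (Timing and content of study measures, Table 1, Comparability of intervention and control group) and not here. Two of the three readings put T1 in the model.

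A reader might also infer that most of any lasting effect is lost. The article does not support that. With T1 as sole covariate it needs r above 0.5 and full persistence; with both scores and equal correlations the share stays below half, and only particular unequal correlations take it higher. Nor would an early benefit go unseen, because it would appear in the T1 analysis.

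The two-phase design (Methods/design) gives T1 adjustment a rationale for a phase II question. That is fair, but hypothesis (6) is not limited to phase II. No second randomization is described, so the increment is not itself a randomized comparison.

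Finally, d = 0.4 was set for a different outcome, so the power figures are illustrative only. That stands; the shares removed do not depend on d.

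**Conclusion.** The concern holds in a conditional form. Read literally, the covariate rule puts a post-intervention score into the T2 models for CWS and HADS, and those models then do not estimate the total effect that hypothesis (6) describes. For a fully sustained effect, equal SDs and an assumed r of 0.3 to 0.8, the loss is about 30–80% with T1 alone, about 23–44% with baseline and T1 under equal correlations, and nil with baseline alone. How many T2 records would also be lost through a missing or omitted T1 cannot be computed from the article.

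The reach is limited: these are secondary outcomes, and the primary outcomes, the sample size and the T1 analysis are untouched. It should be fixed, but it does not threaten the trial's main conclusions.

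**What to change.** Under Secondary research hypotheses, replace the reference to previous scores with the pre-randomization baseline score of the same questionnaire, as covariate at both T1 and T2. If the phase II change is of interest, keep a T1-adjusted T2 analysis but label it supplementary and say that it does not estimate the total effect.

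A mixed model of T1 and T2 on arm, time, arm-by-time and baseline score would serve as well and keeps T2 records when T1 is missing, but it is optional.

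The cost is one sentence. Baseline CWS and HADS are already collected from every participant before randomization, so no data collection or sample size changes. Fixing the covariate in advance also removes a choice that could otherwise be made after the results are seen.
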